### Effectiveness

The effectiveness of the two methods in producing useable recommendations will be evaluated by submitting the adapted recommendations to a panel of 20 potential users (individuals with TBI, clinicians, managers and policymakers). In this study effectiveness is defined as the capacity of a method to produce recommendations that are clear, accurate, appropriate and useful for users to guide their activities. The experts will be blinded to the methods used to adapt the recommendations. They will be recruited from the scientific committee that oversees the larger guideline adaptation process mentioned previously, and from community-based TBI associations similar to the one in which the individuals with TBI participating in the recommendations adaptations will be recruited. They will receive an email including the original recommendations, the recommendations produced by the participants, and a link to a questionnaire in which they will be invited to independently rate the clarity, accuracy, appropriateness and usefulness of each of the four recommendations (two conditions and two recommendations) using 10-point Likert scales
[29]. They will also be invited to provide frank comments to justify their ratings.

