### Analysis

Within-subject analysis using the Wilcoxon signed-rank test
[30] will be performed to compare the acceptability score of the two methods. Feasibility indicators will be reported using descriptive statistics. The effectiveness of the methods as rated by the experts will be compared to the score provided by the experts for the perceived clarity, accuracy, appropriateness and usefulness of the recommendations, using generalized linear models (two methods and two recommendations) (Statistical Package for the Social Sciences (SPSS), Chicago, Illinois, United-States, using generalized estimating equations (GEE) since both independent variables are repeated measures). The selected distribution will depend on the distribution of the data. The statistical analysis will be performed using SPSS 20. All the qualitative data (discussion group and qualitative comments stemming from the questionnaires) will undergo a directed content analysis performed using NVivo 9.0 (QSR International, Burlington, Massachusetts, United-States.

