## Discussion

This pilot trial will be the first to evaluate methods for involving individuals with TBI in CPG development. Given the severe impairments and/or disabilities experienced by individuals with TBI, it is likely that the optimal method could be used with success in other populations with disabilities, such as those living with stroke or spinal cord injury.

This pilot study has some limitations. Indeed, we have chosen a very pragmatic approach to test the two methods of adapting recommendations with a limited number of individuals with TBI. The pragmatic characteristic of our trial is important to test the feasibility of the two methods in a ‘real’ context of guideline adaptation, but it also raises issues. We have chosen not to control our sample for any type of disability (motor, cognitive or sensorial) in order to be representative of the population of individuals with moderate to severe TBI. Nor will we select our sample based on their ease with the use of the technology, so as to avoid eliciting an ‘expert’ group of patients not representative of the TBI population. Individuals with TBI often have disabilities that may influence their participation in the study, as well as their ability to conduct tasks as requested. For example, a participant might simply feel too tired and fall asleep in the middle of a focus group, limiting the interaction with other members of the group. The setting in which the study will take place (association’s office) is a familiar one for the participants, who sometimes visit it daily. This may make participants feel more comfortable and facilitate their involvement in the study. However, although participants will be instructed not to discuss their participation, contamination may occur during the trial. We will instruct the association employee to be sensitive to this issue and invite participants to share their thoughts with us.

Our trial will allow for the use of optimal IPP methods in a larger project of adapting guidelines for the rehabilitation of individuals with TBI. Ultimately the results will inform the science of CPG development and contribute to the growing knowledge about IPP in rehabilitation settings.

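### The expert comparison treats 20 raters as the sample, but each method yields only two texts, so its confidence interval and p-value describe those four texts and not the methods in general

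*Protocol article*

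**What the plan says.** The Effectiveness section of the protocol article defines effectiveness as "the capacity of a method to produce recommendations that are clear, accurate, appropriate and useful". It is measured by "submitting the adapted recommendations to a panel of 20 potential users", who rate "each of the four recommendations (two conditions and two recommendations) using 10-point Likert scales".

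The two intervention sections fix how the four texts arise. Group 1 holds a discussion group on the first recommendation while Group 2 works on the same recommendation in the Wiki. The methods are then swapped and both groups take the second recommendation. Each group has 10 participants (Participants section), and each group uses each method once.

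The Analysis section compares the methods' effectiveness "using generalized linear models (two methods and two recommendations", by GEE, "since both independent variables are repeated measures". Acceptability is analysed separately: "Within-subject analysis using the Wilcoxon signed-rank test".

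The Discussion concludes: "Our trial will allow for the use of optimal IPP methods in a larger project". Its limitations mention the small number of people with TBI, but not that each method produces only two texts.

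**The concern.** The question concerns methods, so the unit that must be replicated is the session that produces a text. There are two such units per method. Twenty experts reading the same four texts measure those texts more precisely, but they add no information on what another discussion group or another Wiki would have produced.

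Method and recommendation are both repeated only within the expert, so the expert must be the cluster in the GEE. Its standard error then contains rater disagreement and leaves out variation between sessions. A clear result would show that these experts distinguish these four texts. Read as a statement about the two methods, it would claim more precision than the design has, and it could carry undue weight when a method is chosen for the larger guideline project.

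**Working it through.** **Inputs from the protocol article.** 20 experts and four texts, two per method (Effectiveness). Two groups with the methods swapped between periods, and one recommendation per period (Intervention 1 and Intervention 2). No alpha, power, text SD or rater SD is given for this comparison.

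**Count.** 2 groups × 2 periods = 4 texts, which matches the article's own figure of four.

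**Variance of the method contrast.** Take rating = expert effect + text effect + residual, with text SD s_t and residual SD s_e. The method difference is the mean of the two Wiki texts minus the mean of the two discussion-group texts, so each text has weight ±1/2 and the expert effect cancels.

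- Text part: 4 × (1/4) × s_t² = s_t²
- Rater part: 4 × (1/4) × s_e²/20 = s_e²/20
- True variance: s_t² + s_e²/20. The expert-clustered GEE estimates only the second term.

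With q = s_t/s_e, the true standard error is √(1 + 20q²) times the reported one, and the type I error of a nominal 5% test is 2 × [1 − Φ(1.96/√(1 + 20q²))].

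| q (assumed) | √(1 + 20q²) | 1.96 / factor | Type I error |
|---|---|---|---|
| 0 | 1.00 | 1.96 | 5.0% |
| 0.1 | √1.2 = 1.10 | 1.79 | 7.4% |
| 0.2 | √1.8 = 1.34 | 1.46 | 14.4% |
| 0.3 | √2.8 = 1.67 | 1.17 | 24.1% |
| 0.5 | √6 = 2.45 | 0.80 | 42.4% |

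**Check by simulation.** At q = 0.5 (variance ratio 0.25), 20,000 runs with the robust standard error rejected in 44.9%, and 300 runs of a fitted GEE in 43.7%. With no text variation the robust test rejected in 7.4%, because 20 clusters are few. The excess over that figure is due to the texts.

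**More experts.** At a variance ratio of 0.10, the formula gives 25.8% with 20 experts. With 200 experts the factor is √(1 + 200 × 0.10) = √21 = 4.58, and the simulated rate is 66.9%. A larger panel shrinks only the term that the GEE already counts.

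**The text as unit.** Four observations with method and recommendation fitted leave 4 − 3 = 1 residual degree of freedom, with a critical t of 12.71. That test held about 5% in simulation but has almost no power, so it does not rescue the comparison.

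**Which contrasts are balanced.** Codes for the four texts:

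| Text | Method | Recommendation / period | Method × recommendation | Group |
|---|---|---|---|---|
| Group 1, discussion, rec. 1 | −1 | −1 | +1 | −1 |
| Group 2, Wiki, rec. 1 | +1 | −1 | −1 | +1 |
| Group 1, Wiki, rec. 2 | +1 | +1 | +1 | −1 |
| Group 2, discussion, rec. 2 | −1 | +1 | −1 | +1 |

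The method column is orthogonal to recommendation/period and to group. The interaction column is the group column with the sign reversed, so intercept, method, recommendation, interaction and group together have rank 4, not 5. In simulation, a pure group difference of 0.5 residual SD with no true interaction made the interaction term significant in 62.7% of runs. The method difference within one recommendation always compares Group 1 with Group 2. Only the average over both recommendations is free of group.

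**The case against.** The best defence is that this is a pilot meant to document, and that the GEE is valid for how experts rate these four texts. That is correct. It leaves the scope of inference as the issue, and the article itself sets that scope by defining effectiveness at the level of the method.

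Four stronger readings are tempting and are not supported.

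- *The method effect is biased.* It is not confounded: the averaged contrast is balanced over group and recommendation/period. The fault is false precision.
- *The interaction in the model is just the group effect.* The article lists two factors and states no interaction term. If one were fitted, it would be aliased with group, and a true interaction would sit in the same contrast. Neither could be identified as the source.
- *The method will be chosen on p < 0.05 from this GEE.* No alpha or decision rule is stated. The sentence on optimal methods rests on the whole trial, including acceptability, preferences, feasibility indicators and qualitative comments.
- *The acceptability test has the same flaw.* Acceptability is each person's own view, and the Wiki is done at home over a week, so equal clustering in both methods is an assumption. With an assumed within-person correlation of 0.4, a session ICC of 0.05 or 0.10 in both methods gives about 13% or 21% type I error. If only the discussion group is clustered, it is about 10% or 13%. With an ICC of 0.01 or 0.02 in both, it is about 6% or 9%. This is a secondary caveat.

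It is also fair to say that the size of the effectiveness problem depends wholly on an assumed ratio, and that at 0.1 it is small. The direction does not depend on it: any text-to-text variation makes the interval too narrow. A separate analysis plan could add a caveat, but it could not add sessions to this design.

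**Conclusion.** The point holds as one about what the expert comparison can support. The analysis fixed in the article yields a standard error for four particular texts, while the quantity it is said to address is a property of the methods. For that quantity the interval is too narrow by a factor of 1.10 to 2.45, and the true error of a nominal 5% test is about 7% to 42%, for assumed text-to-rater SD ratios from 0.1 to 0.5. The result rests on the expert being the GEE cluster, which is inferred from the repeated-measures statement, and on texts varying at all between sessions of one method. Nothing in the article corrects or acknowledges this.

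**What to change.** 1. In Analysis, state that the expert comparison is conditional on the four texts produced, and that its interval reflects variation between raters only.
2. Report the mean rating of each of the four texts, and the method difference averaged over both recommendations, with a confidence interval labelled as rater-based. Do not present its p-value as evidence that one method is more effective in general.
3. If a method-by-recommendation term is fitted, state that it is completely aliased with Group 1 versus Group 2, and that a difference within a single recommendation is confounded with group.
4. In Discussion, add two texts per method to the limitations, and say that the pilot informs the choice of method for the larger project and does not establish the optimal one.
5. For acceptability, show results by group and note possible correlation within sessions.

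The cost is wording in Analysis and Discussion and a more modest conclusion. No new data are needed, and the Trial status section says that recruitment was still being planned, so the change can precede the data.

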### Intervention 2 (experimental): Wiki

Group 2 participants will first be invited to participate in a Wiki. A Wiki is a collaborative writing web application used to create online content that anyone accessing it can edit or add to
[21,22]. The Wiki was chosen as an innovative intervention that would allow participants to be involved in the CPG adaptation process in a place and at a rate best suited to their abilities as persons with TBI, without having to overcome transportation barriers. This could be especially interesting when CPGs are developed on a national basis and potential participants are located far from each other, such as in our case for Canadian rehabilitation services. Finally, there is increasing evidence of the applicability of electronic communication platforms for the population with TBI
[23-26]. Indeed, approximately one person in two with TBI has access to the Internet
[23,24] and around 60% of them use Facebook on a regular basis
[27]. Thus, it is likely that if they are provided with specialized training material
[24], the participants will be able to successfully participate in the guideline adaptation process.

Group 2 participants will receive an invitation by email, to include: 1) instructions about Wiki use, 2) the recommendation to be discussed online (the same one used by Group 1), and 3) a synthesis of the evidence that was used to produce that specific recommendation. The Wiki will be structured to describe the research project and present a synthesis of the evidence that was used to produce that specific recommendation. It will then allow the participants to express their opinion concerning the recommendation and specify their preferences about the recommendation, suggesting potential modifications to make to the recommendation. Support interventions will be provided electronically as needed by the moderator to encourage participants to interact on the Wiki. The participants will also receive prompts from the researchers two, four and six days after the initial email to encourage them to participate in the Wiki. They will have one week to do so.

One week after the end of the first data collection, in accordance with the crossover design, Group 1 participants will be assigned to the Wiki intervention and Group 2 participants will be assigned to the discussion group intervention. The procedure will be repeated with a second recommendation.

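### The expert-clustered GEE supports a comparison of the four texts produced, not of the two methods, because each method yields only two texts and variation between texts is left out of the standard error

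*Protocol article*

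**What the plan says.** The Effectiveness section sets the target: "In this study effectiveness is defined as the capacity of a method to produce recommendations" of good quality. It is assessed by "submitting the adapted recommendations to a panel of 20 potential users", blinded to method, who score "each of the four recommendations (two conditions and two recommendations") on four 10-point items.

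The section on the Wiki intervention shows where the four texts come from. In the first period Group 1 meets as a discussion group while Group 2 uses the Wiki, and Group 2 receives "the recommendation to be discussed online (the same one used by Group 1"). The groups then exchange methods: "The procedure will be repeated with a second recommendation".

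The Analysis section compares the ratings "using generalized linear models (two methods and two recommendations"), "using generalized estimating equations (GEE) since both independent variables are repeated measures". It names no term for the text or for the group that wrote it. The limitations in the Discussion mention the small number of patients, but not that each method yields only two texts.

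**The concern.** The experts measure the texts; the method shows itself only through the texts. Clustering on expert answers this question: would another panel of raters also prefer these texts? The stated definition of effectiveness asks a different one: would the method again produce a better text if it were run afresh? The second question involves text-to-text variation, which the planned standard error does not contain. More experts sharpen the answer to the first question and leave that part of the second untouched.

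What is at stake is the reading of the result. The Discussion expects the trial to inform the choice of involvement method for a larger guideline project and suggests the preferred method may suit other disabled populations. A narrow rater-based interval could be taken as evidence about the methods when it describes only two outputs of each.

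**Working it through.** The article gives no significance level, power or sample-size figure for effectiveness, so there is no figure of its own to reproduce.

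**Inputs from the article.** 20 experts; four texts (2 methods × 2 recommendations), hence two per method; method and recommendation as factors, repeated within expert (Effectiveness, Analysis).

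**Assumptions.** A two-sided 5% level; no true method effect; s_e = residual SD of one expert's rating of one text; s_t = SD between texts after lasting writing-group and recommendation effects are removed; r = s_t/s_e. The article gives neither SD, so r is varied.

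**Step 1: what cancels.** Write g1, g2 for writing-group effects and q1, q2 for recommendation effects.
- Discussion-group texts: g1 + q1 (first period) and g2 + q2 (second period).
- Wiki texts: g2 + q1 (first period) and g1 + q2 (second period).
- Wiki mean minus group mean: (g2 + q1 + g1 + q2)/2 − (g1 + q1 + g2 + q2)/2 = 0.

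The crossover therefore removes these effects from the averaged method contrast. An expert's general severity cancels too, since each expert rates all four texts. Within a single recommendation, however, method and writing group cannot be separated.

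**Step 2: what remains.** The contrast is (mean of 2 texts) − (mean of 2 texts).
- Text part: 4 × (1/2)² × s_t² = s_t².
- Rater part: 4 × (1/2)² × s_e²/20 = s_e²/20.
- Actual variance for a claim about methods: s_t² + s_e²/20.
- Variance estimated by clustering on expert: s_e²/20.

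**Step 3: size.** Ratio of actual to reported standard error = √(1 + 20r²). False-positive rate = 2 × [1 − Φ(1.96/ratio)].

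| r | SE ratio | False-positive rate | Simulated robust Wald test |
|---|---|---|---|
| 0 | 1.00 | 5.0% | 7.2% |
| 0.1 | √1.2 = 1.10 | 7.4% | 9.9% |
| 0.2 | √1.8 = 1.34 | 14.4% | 16.4% |
| 0.3 | √2.8 = 1.67 | 24.1% | 26.1% |
| 0.5 | √6 = 2.45 | 42.4% | 43.1% |

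The simulation used 20,000 trials per value of r, with ratings rounded to 1–10. Its 7.2% at r = 0 comes from the uncorrected robust variance with 20 clusters, which is a separate matter: a rater-level paired t test gave 5.1% there, but still 22.0% at r = 0.3. An actual GEE fit (400 trials) gave 6.5%, 19% and 45% at r = 0, 0.25 and 0.5.

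For scale, text variation as a share of text-plus-residual variance is r²/(1 + r²): 0.01/1.01 = 1% at r = 0.1 and 0.25/1.25 = 20% at r = 0.5.

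**Step 4: more experts.** At r = 0.3 with 40 experts the ratio is √(1 + 40 × 0.09) = 2.14 and the false-positive rate is 36%. The true variance s_t² + s_e²/n does fall as n grows, but never below s_t², while the reported variance falls towards zero.

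**The case against.** The strongest reply is that this is a pilot meant to document three things, and effectiveness is one of them. The article states no hypothesis, significance level or decision rule for it. A reader might infer that the plan commits to choosing a method by the GEE p-value. It does not: no passage ties the choice for the larger project to that result. This lowers the severity. The mismatch between the stated definition of effectiveness and the error term remains, and the article uses a model-based comparison here while reserving descriptive statistics for feasibility.

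A second reply is that the crossover already protects the comparison. In part it does: lasting group and recommendation effects cancel. A reader might count all variation between groups of patients as omitted error, which would overstate the problem. If, for illustration, half of a given text variance were lasting group variance, the rates computed from totals of 0.2, 0.3 and 0.5 would fall from 14%, 24% and 42% to about 10%, 16% and 30%. That is why s_t is defined net of those effects. Balance is not replication, though: there are still two texts per method.

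A third reply is that the GEE is valid for what it estimates. That is right for these four texts over raters, and the fix keeps that use.

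Leaving the model to an analysis plan does not answer the point, because the article itself fixes both the number of texts and the repeated-measures structure.

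**Conclusion.** The point holds as a limit on what the effectiveness analysis can show. Three features fixed in the article establish it: a method-level definition, two texts per method, and experts as the independent units. The resulting error bar is right for these four texts and too narrow for the methods whenever s_t exceeds zero.

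The size is not established. A reader might infer that the test runs at several times its nominal level. The article supplies neither the level nor s_t. The rate is 5% if texts do not vary beyond group and recommendation, about 7% at r = 0.1, and reaches roughly three times 5% only from about r = 0.2. These rates are illustrative.

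Nor do the documents support replacing the GEE interval with a text-level one on the two Wiki-minus-group differences. Its single degree of freedom is the writing-group contrast, so it would use as error an effect that cancels from the method estimate.

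This should be fixed. It does not invalidate the trial.

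**What to change.** In Analysis, do not use the GEE p-value as a test of method. Report:
- the mean rating of each of the four texts;
- the Wiki-minus-group difference for each recommendation;
- the average of those two differences with a rater-based 95% CI labelled 'for these four texts, over raters'.

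In Analysis and Discussion, state that there are two texts per method, that within each recommendation the method is confounded with the writing group, and that effectiveness is described for these texts and not tested for the methods in general. Do not add a 1-degree-of-freedom text-level interval.

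The cost is wording only. Design, data collection and panel are unchanged, and the GEE may still supply the rater-based interval. The downside is a weaker effectiveness claim, which fits a pilot whose goal is to document. Recruitment was still being planned at submission (Trial status), so the change could be made before any ratings were seen.

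### GEE on at most 20 experts, with no small-sample correction named: about 7% false positives at a nominal 5% if the usual uncorrected Wald test is used

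*Protocol article*

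**What the plan says.** Under Effectiveness, the protocol article describes "submitting the adapted recommendations to a panel of 20 potential users". Each expert rates "each of the four recommendations (two conditions and two recommendations) using 10-point Likert scales", on four scales, so each expert gives four ratings per scale, and a full panel gives 20 × 4 = 80.

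Under Analysis, these ratings are to be compared by generalized linear models with method and recommendation as the two factors, "using generalized estimating equations (GEE) since both independent variables are repeated measures". It adds: "The selected distribution will depend on the distribution of the data". The software is SPSS 20.

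The article does not name a variance estimator, test statistic, working correlation, significance level or small-sample correction for this comparison. It gives no list of candidate distributions and no rule for choosing among them.

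**The concern.** The sandwich variance used with GEE is justified when the number of independent clusters is large. Here the clusters are the experts, so there are at most 20, and fewer if some do not reply. The 80 ratings per scale do not help, because method and recommendation both vary within expert. With few clusters the uncorrected sandwich variance is too small on average. The normal reference also ignores the uncertainty in that variance. Both faults act in the same direction: p-values too small and intervals too narrow.

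This is the only inferential analysis of effectiveness, one of the pilot's three aims, and the Discussion says the trial will inform the choice of method in a larger guideline project. A chance difference between Wiki and discussion group could carry forward.

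Leaving the distribution to the data raises a separate issue. A normal model with identity link estimates a difference in means, and a gamma model with log link estimates a ratio of means. Until the family and link are fixed, so is neither the effect measure nor its interval.

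**Working it through.** The article states no error rate, power or significance level for this comparison, so there is no figure of its own to reproduce.

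**Inputs from the article:** 20 experts; 2 methods × 2 recommendations per expert; GEE.

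**Assumptions, not in the article:** uncorrected sandwich variance, normal or chi-square Wald test, two-sided 5%, identity link, approximately normal within-expert differences. Non-response is shown as a range.

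**Step 1: reduce to differences.** For expert i, let dᵢ be the mean Wiki rating minus the mean discussion-group rating over the two recommendations. In this balanced layout the GEE method effect is the mean difference d̄, and its uncorrected sandwich variance is Σ(dᵢ − d̄)²/n². The paired t statistic uses Σ(dᵢ − d̄)²/[n(n−1)] instead. Hence

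z = t × √[n/(n−1)],

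and rejecting when |z| > 1.960 is the same as rejecting when |t| > 1.960 × √[(n−1)/n].

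**Step 2: actual size.** For n = 20 the cut-off is 1.960 × √(19/20) = 1.910, and P(|t₁₉| > 1.910) = 7.13%. If the variance divides by n−1 but the reference stays normal, the size is P(|t₁₉| > 1.960) = 6.48%.

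| Responding experts | Size, n divisor | Size, n−1 divisor | Coverage of 95% interval (n divisor) |
|---|---|---|---|
| 20 | 7.1% | 6.5% | 92.9% |
| 18 | 7.4% | 6.7% | 92.6% |
| 16 | 7.7% | 6.9% | 92.3% |
| 10 | 9.6% | 8.2% | 90.4% |

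**Step 3: interval width at n = 20.** Uncorrected over exact: 1.910/2.093 = 0.913, about 9% too narrow. The other way round, (2.093/1.960) × √(20/19) = 1.096, so the corrected interval is about 10% wider.

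**Step 4: simulation under no method effect.** Ratings were integers from 1 to 10 for 20 experts. Assumed SDs were 1.2 between experts, 0.6 expert-by-method and 1.3 residual.

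- Closed form, 100,000 runs at each of three mean ratings (5.5, 7 and 8.5): uncorrected robust z gave 6.96% to 7.14%; the paired t-test on 19 df gave 4.8% to 5.0%.
- Full GEE fits with exchangeable correlation, 1,500 runs at mean 7 (Monte Carlo SE about 0.7 points): normal 7.7%, gamma-log 7.4%, Poisson-log 7.3%.
- Bias-reduced sandwich with t₁₉, same 1,500 runs: 4.3% (Monte Carlo SE about 0.6 points).
- Model-based standard error with z, same runs: 8.5%.
- Smallest p-value over the three families: 7.9%, against 7.7% for normal alone.

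**The case against.** The strongest reply is that the premise is supplied from outside. The article names GEE and SPSS 20 and nothing more about the inference. It condenses a fuller plan that is not shown, and a variance correction is the kind of detail left to such a plan. Corrected versions of GEE fit the article's wording and do not inflate the error: the bias-reduced sandwich with t₁₉ gave 4.3%, and a score-type test works out at about 4.7%. This stands, and it makes the 7.1% conditional. What remains is that the article commits to a large-sample method for 20 clusters, when a simple paired analysis of the same ratings has the right size at almost no cost.

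Three stronger readings are tempting, and the documents support none of them.

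- **That every analysis under this plan is anti-conservative.** The corrected versions above show otherwise.
- **That choosing the distribution from the data materially inflates false positives.** Even taking the smallest of three p-values added only 0.2 points (7.9% against 7.7%). The sentence may also mean matching the family to the pooled shape of the ratings, without looking at the method contrast. The case for fixing it is pre-specification of the effect measure.
- **That the error over the four scales measures this defect.** Four independent tests at a true 5% already give 1 − 0.95⁴ = 18.5%. Most of any such total is ordinary multiplicity, and four related scales rated by the same experts are unlikely to be independent.

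It can also be said that this is a pilot with no power claim or decision threshold for the ratings, which are read beside the experts' comments. That is fair, and it keeps the point modest.

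**Conclusion.** The point holds conditionally. Under uncorrected Wald inference at two-sided 5%, the expert comparison has a false-positive rate of about 7.1% with 20 experts (6.5% with an n−1 divisor), rising to 7.7% with 16 responders and 9.6% with 10. With 20 experts, 95% intervals cover about 92.9% and are about 9% too narrow. The variance estimator, the test and the 5% level are assumptions; the cluster count and GEE are the article's. The excess of 1.5 to 2 points with a full panel is modest, but it is avoidable by a change of wording and worth removing before any ratings exist. The open choice of distribution is a gap in specifying the effect measure and has little bearing on the error rate.

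**What to change.** For each of the four scales, compute each expert's mean Wiki rating minus mean discussion-group rating over the two recommendations. Analyse it with a paired t-test and t-based interval on n−1 degrees of freedom, where n is the number of experts who respond. Add a Wilcoxon signed-rank test as sensitivity.

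If GEE is preferred, keep it with a bias-corrected sandwich variance and a t reference on n−1 degrees of freedom.

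A linear mixed model is equivalent to the paired t-test only if it includes an expert-by-method random effect. With a random intercept alone, simulated size was 7.8% at an expert-by-method SD of 0.6 and nearly 11% at 0.9, while the paired t-test stayed at 5%.

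Replace the sentence on the distribution with a named distribution and link, or with a rule that chooses them on pooled ratings with method masked.

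The cost is wording in the analysis plan and intervals about 10% wider than uncorrected ones. According to Trial status, the team was still preparing tools and planning recruitment at submission, so at that stage the change could precede any data.
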